### Informed consent

Eligible patients may only be included in the study after providing written (witnessed, where required by law or regulation), informed consent, or, if incapable of doing so, after such consent has been provided by a legally acceptable representative of the patient. Informed consent will also be taken from the individual who accompanies a patient to the assessment visits – whether that is their carer, parent, partner or someone who knows them well – as they will be asked to complete assessments at various time points.

### Randomisation and blinding

Randomisation will be carried out by the South East Wales Trials Unit, using a computer-generated allocation sequence according to a 2:1 for intervention-to-control ratio. The participant’s unique identification number and allocation will be double-blinded so that the participant, clinician, research psychologist and trial statistician will not know to which treatment group the participant has been allocated.

The trial pharmacy will hold details of patients’ treatment allocations and can maintain 24-h cover to unblind in case of an overdose. For all other emergencies, physicians should stop the drug (as unblinding would not affect symptom management) and contact a member of the clinical team as soon as possible afterwards. For non-emergencies, the treating physician should contact a trial clinician to discuss the need to unblind or stop treatment.

### Treatment

The daily investigational drug dose will be 5 mg of everolimus administered for 6 months as two oral 2.5-mg tablets once daily, but with adjustment to achieve trough blood levels of 3–10 ng/ml. A lower dose (as compared with the dose used to treat renal angiomyolipoma [AML]) has been chosen to mitigate side effects, whose frequency and severity may be dose-related. The appearance of placebo medication will be identical to that of active drug to maintain the blinding. Pharmacy staff will be unblinded and will not reveal treatment allocation to anyone without permission from a member of the clinical team or investigational team. Trough blood levels of everolimus will be measured at each study visit and reported to the study doctor through the trials unit. Mock levels for patients on placebo will also be reported in proportion to those for patients on active drug. The study clinicians will then make decisions regarding dosage changes.

Treatment will be dispensed at visits 2, 4 and 6. Patients will take the medication at the study site at visits 3–7 and at home on all other treatment days. Compliance will be monitored by pill counts at each visit. Samples for drug levels (pharmacokinetic assessments) will be taken at visits 3–7 inclusive.

### Safety information and clinical management

Adverse events (AE) are defined as the appearance or worsening of any undesirable sign, symptom or medical condition occurring after starting the study drug or placebo, even if the event is not considered to be related to the investigational medicinal product (IMP). The most common AE are listed in Table 2, and further information on frequency categories of adverse reactions is reported in Additional file 2.

**Table 2 Tab2:** Common adverse events

Most frequently observed AE resulting from study drug	Most frequently observed laboratory abnormalities
Mouth ulcers	Neutropenia
Rash	Thrombocytopenia
Infections	Hypercholesterolemia
Diarrhoea	Hypertriglyceridemia
Fatigue	Hypophosphatemia
Headache	
Anorexia	
Nausea	
Vomiting	
Non-infectious pneumonitis	

*AE* adverse events

All AE will be collected, recorded and reported in accordance with good clinical practice and the requirements of the Medicines for Human Use (Clinical Trials) Regulations 2004. Their severity will be graded according to the CTCAE. Once detected, they will be treated appropriately and monitored until resolution, unless deemed by the investigator as not necessary and documented accordingly. Treatment may include interruption, modification or discontinuation of study drug treatment and changes in the frequency or nature of assessments, hospitalisations or any other medically required interventions. Recommended treatment of side effects is detailed in Additional file 3.

Known common side effects of the IMP are listed in the summary of product characteristics (SmPC), which is the reference safety information (RSI) for this trial. Any new relevant information between SmPC updates will be issued in the form of investigator notifications. On the basis of the approved RSI for everolimus, expected AE in patients with tuberous sclerosis are seizures and haemorrhage from AML; additional expected AE in females with lymphangioleimyomatosis complicating TSC are pneumothorax, chest infection, chylothorax and haemoptysis.

AE the nature and severity of which are consistent with the information set out in the SmPC for everolimus will be considered expected. Events ongoing at study completion will be followed as clinically indicated. Furthermore, effects of the study drug may be influenced by products that affect cytochrome P450 3A4 and/or P-glycoprotein. These will be avoided wherever possible or used with caution and documented accordingly.

### Pregnancy

Eligible participants are advised that it is not recommended to become or to make their partners pregnant whilst on, and until 30 days after stopping, the study drug. Pregnancies will be reported and documented as appropriate, and followed to determine outcome, including spontaneous or voluntary termination; details of the birth; and the presence or absence of any birth defects, congenital abnormalities or maternal and/or newborn complications. A pregnancy in the partner of a male participant occurring up to 3 months after stopping the study drug will be reported to the sponsor as soon as possible after consent to report information regarding pregnancy outcome has been obtained from the mother.

### Outcome measures

The neurocognitive measures listed in Table 3 will be used at various study visits (see the neuropsychological assessment schedule in Additional file 4 for full details). Although the test battery at some visits is extensive, patients who have neurocognitive problems will complete only the earliest stages of many tests and will therefore complete their assessments much more quickly than the “maximum times” listed in Table 3. A similar test battery has been used with patients with TSC in a previous study [14].

**Table 3 Tab3:** Neurocognitive outcome measures

	Name of measure
Eligibility visit screening measures	Wechsler Abbreviated Scale of Intelligence (four subtests) [17]
	Edinburgh Handedness Inventory [18]
Primary outcome measures	Complex Figure test and List Learning test from the BIRT Memory and Information Processing Battery [20]
	Spatial Working Memory and Stockings of Cambridge from the CANTAB [21]
	Telephone search dual task from the Test of Everyday Attention [22]
Secondary outcome measures	Information Processing Battery, spatial span and attentional set-shifting (IDED) from the CANTAB [21]
	Cancellation task and Verbal Fluency from the Controlled Oral Word Association Test [23]
	Symptom Checklist-90-Revised [24]
	Quality of Life in Epilepsy [25]
	Liverpool Seizure Severity Scale [26]
	Vineland Adaptive Behaviour Scales-II (survey form) [27]
	Social Responsiveness Scale – Adult version [28]
	Social Communication Questionnaire [29]
	National Adult Reading Test [19]

*Abbreviations: BIRT* Brain Injury Rehabilitation Trust, *CANTAB* Cambridge Neurocognitive Test Automated Battery, *IDED* intra-dimensional/extra-dimensional

### Study assessments

The timing of assessments required during the study is delineated in the study assessment schedule shown in Additional file 5. Appointments will be postponed and rescheduled for patients who have had a generalised tonic-clonic seizure within 48 h of scheduled neurocognitive testing or a complex partial seizure within 24 h of scheduled neurocognitive testing. At the screening visit, background, demographic and administrative assessments will be carried out which will include relevant medical history/current medical conditions; a physical examination; and blood laboratory examinations as per protocol, including a hepatitis screen and a pregnancy test. Patients will also be assessed for IQ [17], handedness [18] and pre-morbid intellectual function [19]. The clinician will also ascertain eligibility by evaluation based on the inclusion and exclusion criteria of the study.

Following the screening visit (visit 1), eligible patients will be scheduled for the baseline and randomisation visit (visit 2) approximately 4 weeks later. This will be considered week 0, and treatment will commence. As outlined in the study assessment schedule (Additional file 5), patients will then be followed for 6 months, with study visits taking place at week 2 (safety), week 4 (safety, some neurocognition), week 6 (safety), week 12 (full neurocognition) and week 24 (full neurocognition at the end of the treatment phase). Each of these visits will take place within 12 h after the last drug administration. A further assessment will be carried out 12 weeks after the end of the last drug or placebo administration, at week 36. Patients will visit the study site on the required days and may stay overnight if travelling from afar, though no hospitalisation will be required. It is anticipated that regular contact with participants and carers will offer the opportunity to address any issues which may contribute to attrition.

Safety assessments will include physical examinations, vital signs and standard clinical laboratory evaluations of haematology, blood chemistry, urinalysis, AE and serious adverse event (SAE) monitoring at each site visit. Monitoring by telephone will be carried out by the clinical trial team at 1 week after initiation of treatment and each month thereafter during the treatment phase of the study, unless a study visit takes place during that calendar month. See Additional file 5 for a full breakdown of the study assessment schedule.

Efficacy assessments for memory (verbal recall memory and non-verbal recall memory) will be measured using two tests that have been validated in the U.K. population across the age range required for this study and for which multiple parallel forms are available as required for retesting. Attentional/executive function will be measured using two tests from a similarly standardised computerised battery, and another from a further well-validated ‘pen-and-paper’ test battery.

Verbal recall memory will be assessed using the list learning recall task [20]. Non-verbal recall memory will be assessed using the complex figure recall task [20]. Attentional/executive function will be assessed using the Stockings of Cambridge [21] planning task and the Spatial Working Memory test [21], and also using the dual task [22].

Attention will be assessed by using the Rapid Visual Information Processing test, the visual search task, sustained listening tasks [22] and the cancellation task [23]. Executive function will be assessed by using the non-verbal intra-dimensional/extra-dimensional test [21] and the verbal Controlled Oral Word Association Test/FAS test [23]. The spatial span task will assess simple working memory. The Symptom Checklist-90-Revised [24] will be used to assess psychological problems and symptoms of psychopathology and/or psychiatric issues.

The Quality of Life in Epilepsy Inventory [25] will be used to evaluate overall quality of life. Seizure severity will be assessed by using the Liverpool Seizure Severity Scale [26] and a seizure diary. A carer, relative or friend will complete the Vineland Adaptive Behaviour Scales-II [27], the Social Responsiveness Scale – Adult version [28] to assess any autism spectrum symptoms, and the Social Communication Questionnaire [29]. All scheduled safety and outcome assessments will be done at the Clinical Research Facility at the University Hospital of Wales, Cardiff. This facility has a dedicated neurocognitive testing suite.

### Data management and monitoring

Data will be captured on study-specific case report forms (CRFs). CRFs will not constitute source data, and all data entered on the CRFs will be traceable to an original source record (electronic or paper), either as part of the electronic database or in the patient’s file. All data management procedures will be detailed in the trial-specific data management plan.

The sponsor’s monitoring standards will ensure 100 % verification for the presence of informed consent, adherence to the inclusion and exclusion criteria, documentation of SAE, and recording of data that will be used for all primary variables. Additional checks of the consistency of the source data with the CRFs will be performed according to the study-specific monitoring plan. All data will be kept for 15 years, in line with the sponsor’s research governance framework regulations for clinical research. Data will be anonymised and stored confidentially in accordance with the Data Protection Act 1998 on password-protected servers maintained in the Cardiff University network.

A Data Monitoring Committee (DMC) will be established that will consist of an independent chair and two other independent members. The main role of the DMC will be to safeguard the interests of the trial’s participants, review the data periodically and make recommendations to the Study Steering Committee.

### Statistical methods

#### Main analysis

All randomised participants who received at least one dose of study drug will be included in the data analysis. Patients will be analysed according to the treatment they received. We will present data descriptively and determine effect sizes. Results will be presented split by trial arm.

The primary outcome of this study is memory function with improved memory function classed as a 1-SD response on any of the memory tests listed in Table 3. A one-sample chi-square test will be used to determine whether the proportion of patients in the intervention group with improved recall memory at 6 months by 1 SD is at least 0.35. The effect size will be presented alongside a 95 % CI and *p* value. The proportion of patients in the control group displaying improved functioning by 1 SD will be used to highlight the learning effect.

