### Screening for eligibility

Entry into the study is carried out through a two-stage process. Those who are likely to be eligible will be offered a screening appointment (visit 1), at which fully informed written consent will be obtained. A screening assessment to confirm or refute eligibility will include a full medical history; current medications; physical examination; blood, urine and (for females) pregnancy tests; and neurocognitive tests. Patients must fulfil all of the inclusion criteria and none of the exclusion criteria, as detailed in Table 1.

**Table 1 Tab1:** TRON study entry criteria

	Inclusion criteria	Exclusion criteria^a^
1	Definite TSC based on current clinical criteria [29]	Prior treatment with an mTOR inhibitor
2	Male or female aged 16–60 years	Investigational agent taken <30 days prior to randomisation
3	IQ >60 as determined by using WASI and able to participate in direct neuropsychological tests	Surgery in last 2 months
4	A score falling on, or below, the 5th percentile (approximately equivalent to −1.5 SD) in one or more of the primary outcome measures	Previous brain neurosurgery, with the exception of sub-ependymal giant cell astrocytoma removal surgery or radiosurgery 5 or more yearsv ago
5	Calculated GFR >60 ml/min/1.73 m^2^, except in case of renal impairment associated with TSC kidney disease, in which event a calculated GFR should be ≥30 ml/min/1.73 m^2^	Significant haematological abnormality (i.e., haemoglobin <8 g/dl, platelets <80,000/mm^3^, absolute neutrophil count <1000/mm^3^)
6	INR ≤1.5 (anti-coagulation permitted if target INR on stable dose of warfarin or LMW heparin for >2 weeks at time of randomisation)	Urine protein/creatinine >0.02 g/mmol, except in case of renal impairment associated with TSC kidney disease, in which case urine protein/creatinine ratio should be >0.1 g/mmol for exclusion
7	Adequate liver function as shown by serum bilirubin ≤1.5 times ULN, ALT and AST ≤2.5 times ULN	Serum creatinine >1.5 times ULN, except in cases of renal impairment associated with TSC complication of kidneys, where serum creatinine should be >300 μmol/L for exclusion
8	If sexually active, negative pregnancy test in females at the time of informed consent, contraception for males and pre-menopausal females in the study	Uncontrolled hyperlipidaemia (fasting cholesterol >300 mg/dl or >7.75 mmol/L and fasting triglycerides >2.5 times ULN, or diabetes with fasting serum glucose >1.5 times ULN)

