9	Seizure-free or stable seizures as defined by no change in type of AEDs in 6 months prior to full recruitment and randomisation at baseline; doses of drugs may have been changed in the 6 months prior to recruitment	History of myocardial infarction, angina or stroke related to atherosclerosis, or any other significant cardiac disease, HIV seropositivity, organ transplant, malignancy other than squamous or basal cell skin cancer
10	Hepatitis B surface antigen-negative, hepatitis C antibody-negative	Lymphangioleiomyomatosis with FEV_1_ < 70 % of predicted, or any other restrictive pulmonary disease
11	All patients must be able to communicate well with the investigator, to understand and comply with the requirements of the study, and to understand and sign the written informed consent form	Bleeding diathesis or on oral anti-vitamin K medication other than low-dose warfarin
12	Female patients of childbearing potential must be prepared to use two acceptable methods of contraception (e.g., intra-uterine device plus condom, spermicidal gel plus condom, diaphragm plus condom) from the time of screening	Pregnancy/lactation
13		Live vaccine required during trial
14		Use of strong inhibitor of CYP3A4
15		Use of strong inducer of CYP3A4, except for anti-epileptic drugs
16		Intercurrent infection at time of randomisation
17		Inability to complete study materials (outcome measures) in English
18		History of significant trauma-related cognitive deficit
19		Impairment of gastrointestinal function or gastrointestinal disease that may significantly alter the absorption of everolimus (e.g., pancreatic insufficiency)
20		Known sensitivity to everolimus or other rapamycin analogues or to its excipients
21		Inability to attend scheduled visits

*Abbreviations: AED* anti-epileptic drug; *ALT* alanine aminotransferase, *AST* aspartate aminotransferase, *CYP3AE* cytochrome P450 3AE, *FEV*
_*1*_ forced expiratory volume in 1 second, *GFR* glomerular filtration rate, *INR* international normalised ratio, *LMW* low molecular weight, *mTOR* mammalian target of rapamycin, *TSC* tuberous sclerosis complex, *ULN* upper limit of normal, *WASI* Wechsler Abbreviated Scale of Intelligence

^a^Patients meeting any of the exclusion criteria will be excluded from entry into or continuation in the study unless sponsor approval is obtained

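### Efficacy is grouped by treatment received rather than by randomised arm, and the Table 1 footnote could cost week 24 outcomes for treatment-related reasons

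*Protocol article*

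**What the plan says.** **Who is analysed, and in which group.** The Main analysis section of the protocol article defines the population: "All randomised participants who received at least one dose of study drug will be included in the data analysis". The next sentence gives the grouping: "Patients will be analysed according to the treatment they received". Results are then to be split by trial arm, without saying whether that means the arm assigned or the arm received. No separate rule is given for efficacy and for safety, and the primary outcome follows directly under the same heading.

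**What these groups are used for.** The primary result is the proportion improved by 1 SD in the everolimus arm at 6 months. The placebo proportion is used to show the learning effect. Secondary analyses adds adjusted differences between the arms, with 95% confidence intervals and p values.

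**Who stays in the study.** The footnote to the exclusion column of Table 1 reads: "Patients meeting any of the exclusion criteria will be excluded from entry into or continuation in the study unless sponsor approval is obtained". Two of the criteria it covers are "Significant haematological abnormality (i.e., haemoglobin <8 g/dl, platelets <80,000/mm^3^, absolute neutrophil count <1000/mm^3" and "Uncontrolled hyperlipidaemia (fasting cholesterol >300 mg/dl or >7.75 mmol/L and fasting triglycerides >2.5 times ULN". Under Safety information and clinical management, adverse events may lead to interruption, modification or discontinuation of study drug. Nothing there says that the patient then leaves the study.

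**The concern.** Treatment received is a usual basis for safety tables. As the only basis for efficacy it gives up the protection of allocation, which the article says is made "using a computer-generated allocation sequence according to a 2:1 for intervention-to-control ratio". The trial is not powered for a formal comparison of the arms, but it exists to supply effect sizes for later trials. Both the between-arm estimates and the reading of placebo as the learning effect assume that the groups are those formed by randomisation.

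The footnote raises a different problem. By covering continuation as well as entry, it applies laboratory thresholds after treatment has begun. Some of these concern abnormalities of the kind Table 2 lists. If a patient who crosses a threshold leaves the study, the 6-month outcome may not be collected. Such losses could be more frequent on everolimus than on placebo, and the primary proportion would then describe a selected part of the everolimus arm.

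**Working it through.** **1. The plan's own sample size.** Inputs from Sample size determination: null proportion 0.15, alternative 0.35, one-sided alpha 0.05, power 80%, 20% loss to follow-up, 2:1 allocation.

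n = [(1.645 × √(0.15 × 0.85) + 0.842 × √(0.35 × 0.65)) / (0.35 − 0.15)]² = 24.44, rounded up to 25.

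25 / 0.8 = 31.25, rounded up to 32 on everolimus; 32 / 2 = 16 on placebo; total 48. The stated figure is reproduced.

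**2. Effect of grouping by treatment received.** Suppose one patient receives the wrong treatment. The article gives no error rate. The starting counts, 3/16 = 0.188 on placebo and 10/32 = 0.313 on everolimus, are assumed.

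| Patient moved | Placebo | Everolimus |
|---|---|---|
| Placebo to everolimus, non-responder | 3/15 = 0.200 | 10/33 = 0.303 |
| Placebo to everolimus, responder | 2/15 = 0.133 | 11/33 = 0.333 |

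The placebo proportion moves by 1.3 or 5.4 points, the everolimus proportion by 0.9 or 2.1 points.

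**3. Footnote against Table 2.**

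| Exclusion criterion | Entry in Table 2 |
|---|---|
| Neutrophils <1000/mm³ | Neutropenia |
| Platelets <80,000/mm³ | Thrombocytopenia |
| Uncontrolled hyperlipidaemia at the stated cholesterol and triglyceride limits | Hypercholesterolemia, hypertriglyceridemia |

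The overlap is in kind. Table 2 gives no grade or frequency. These entries are in its laboratory column, beside the column headed "Most frequently observed AE resulting from study drug".

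**4. Effect of lost week 24 outcomes.** The number lost is not given, so this is illustration only. Start from 8 responders among 25 evaluable everolimus patients, 8/25 = 0.320. This lies between 0.15 and 0.35, the range the article leaves to discussion by the trial team.

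- One, two or three non-responders lost: 8/24 = 0.333, 8/23 = 0.348, 8/22 = 0.364. The third loss passes 0.35.
- Three lost without regard to response: expected responders lost 3 × 0.32 = 0.96, so (8 − 0.96)/22 = 0.320. No bias.
- Three responders lost: 5/22 = 0.227.

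On the full arm of 32, losing four non-responders (4/32 = 12.5%, inside the 20% allowance) turns 10/32 = 0.313 into 10/28 = 0.357.

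The direction and size of any bias therefore depend on who is lost, which the document cannot tell us.

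**The case against.** **The grouping rule may hardly matter.** Placebo looks identical to active drug, and participants, clinicians, the research psychologist and the trial statistician are blinded. There is no crossover or open-label arm. A reader might infer that patients who stop everolimus early would be counted as controls, but they have still received everolimus. The two groupings differ only through dispensing errors, and the primary test is one-sample. This stands, and it limits the size of the point. It does not supply the missing as-randomised efficacy analysis.

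**The footnote does not delete anyone from the analysis.** A reader might infer that it does. Main analysis keeps every randomised patient with at least one dose, so harm can come only through missing 6-month outcomes. Rules for handling missing data may properly sit in a statistical analysis plan that is not shown. The wording on continuation, however, is stated here.

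**Stronger readings that the document does not support:**

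- That the footnote takes out chiefly everolimus patients. No frequency of these abnormalities at the exclusion thresholds is given.
- That on-treatment infections trigger it. That criterion is tied to the time of randomisation.
- That the sponsor-approval clause contradicts the eligibility text. That text reads "Patients must fulfil all of the inclusion criteria and none of the exclusion criteria, as detailed in Table 1", and the footnote belongs to that table.
- That the false-positive rate is inflated by a known amount. This would need both a loss rate and the assumption that every lost patient is a non-responder.

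**Conclusion.** The point holds in a limited form, as two separate matters of wording.

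- **Grouping.** Efficacy is assigned to treatment received, with no analysis by randomised arm. This follows directly from the text. The expected numerical effect is small. It bears mainly on the secondary between-arm estimates and on the placebo proportion, where one misdispensed patient could shift the result by roughly 1 to 5 points under the assumed 3/16.
- **Continuation.** The footnote may end follow-up for reasons related to treatment, and so may bias the everolimus response proportion. The size is unknown. The move from 0.32 to 0.36 rests on assumed counts and on all three lost patients being non-responders. If loss is unrelated to response there is no bias, only lost precision.

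Both are worth correcting because the proportion is read against a threshold of 0.35 and the effect sizes are meant to inform later trials.

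**What to change.** 1. In Main analysis, state that efficacy is analysed by randomised arm in all randomised patients who took at least one dose, and that safety is analysed by treatment received.
2. Reconcile the continuation wording of the Table 1 footnote with Safety information and clinical management, which provides for stopping study drug, and with Main analysis, which includes everyone dosed. The result should separate stopping study drug from leaving the study, so that week 24 and week 36 assessments are still collected and analysed after drug is stopped. This concerns follow-up and analysis only; no clinical stopping rule is proposed.

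The cost is a few sentences of protocol and analysis-plan text, and follow-up of any off-drug patients at visits already scheduled. The sample size is unchanged at 32 + 16 = 48.

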### Sample size determination

The sample size has been calculated on the basis of Fleming’s single-stage procedure [16] and considers the sample size required to assess the change in the experimental group. The control group provides evidence of the learning effect due to repeated assessments. The proposed study seeks to determine effect sizes in relation to the primary outcome measures to enable informed designing of subsequent larger studies. This study is therefore not powered for formal statistical comparison of placebo and study drug groups.

We estimate the learning effect (i.e., the proportion of patients whose memory function improves due to familiarity with the assessments) to be slightly less than 0.15. A proportion of less than 0.15 in the intervention group would therefore indicate that the intervention (everolimus in the treatment of neurocognitive problems in tuberous sclerosis) does not warrant further investigation. A proportion of at least 0.35 would provide sufficient evidence for further investigation of this intervention. Values between these would be discussed in depth by members of the trial team.

Therefore, to test the null hypothesis that the proportion of patients in the intervention group who improve their memory function by 1 SD is at most 0.15 against the alternative hypothesis that the proportion of patients in the intervention group who improve their memory function by 1 SD is at least 0.35, with 80 % power and a one-sided α of 0.05, we require a total sample size of 48 (i.e., 32 who receive the intervention and 16 control subjects). This sample size is inflated to allow for 20 % loss to follow-up.

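### The primary test is stated against 0.35, but the trial was sized to reject 0.15, so the planned p value addresses the wrong hypothesis

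*Protocol article*

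**What the plan says.** Sample size determination in the protocol article names its method ("The sample size has been calculated on the basis of Fleming’s single-stage procedure") and both hypotheses. The null is that "the proportion of patients in the intervention group who improve their memory function by 1 SD is at most 0.15". The alternative is that "the proportion of patients in the intervention group who improve their memory function by 1 SD is at least 0.35". The error rates are given as "with 80 % power and a one-sided α of 0.05". The result is 32 everolimus and 16 control patients, with the remark that "This sample size is inflated to allow for 20 % loss to follow-up". The same section puts the learning effect at slightly below 0.15. It also gives cut-offs for the decision: below 0.15 no further work, 0.35 or more sufficient, and anything between to be discussed by the trial team.

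Main analysis, under Statistical methods, says what the one-sample chi-square test is for: "determine whether the proportion of patients in the intervention group with improved recall memory at 6 months by 1 SD is at least 0.35". A 95% CI and a p value are to accompany the estimate. The figure 0.15 appears nowhere in the statistical methods.

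**The concern.** A one-sample chi-square test needs one reference proportion, and its p value refers to that proportion. The analysis text supplies only 0.35, which is the design alternative. An analyst following that text would enter 0.35 as the expected proportion, and the test would then have a different null from the one the trial was sized on.

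The null of 0.15 stands for improvement from familiarity with the tests. The control arm is described only as illustrating that effect, and the trial is expressly not powered to compare the arms. Rejecting 0.15 is therefore the only formal test that everolimus patients improve more often than practice would explain. A p value against 0.35 does not answer that question, and the stated alpha and power do not apply to it.

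**Working it through.** **Inputs (Sample size determination).** p0 = 0.15, p1 = 0.35, one-sided alpha 0.05 (z = 1.645), power 80% (z = 0.842), loss 20%, allocation 2:1.

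**1. Reproduce the plan's size.** The single-stage normal approximation is

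n = [(1.645·√(0.15·0.85) + 0.842·√(0.35·0.65)) / (0.35 − 0.15)]² = 24.44, so 25.

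25/0.8 = 31.25, so 32. Adding 16 controls gives 48, which matches. A one-sided alpha of 0.025 would give 31, then 39, which does not. The size therefore rests on rejecting 0.15 at one-sided 0.05.

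**2. Method for the tests.** The signed root of the one-sample chi-square is z = (x/n − p)/√(p(1 − p)/n), where p is the reference value. The critical count is the smallest x with z above 1.645 (one-sided 0.05) or 1.96 (upper side of a two-sided 0.05 test). Probabilities are exact binomial tails. I use n = 25 (evaluable after the planned loss) and n = 32 (all randomised to everolimus).

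**3. Chance of a significant result when the true proportion is 0.35.**

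| Reference value | n | Test | Needs | Probability |
|---|---|---|---|---|
| 0.35 | 25 | one-sided chi-square | ≥13 | 6.0% |
| 0.35 | 25 | upper side of two-sided, or exact one-sided | ≥14 | 2.5% |
| 0.35 | 32 | one-sided chi-square | ≥16 | 5.8% |
| 0.35 | 32 | upper side of two-sided, or exact one-sided | ≥17 | 2.7% |
| 0.15 | 25 | one-sided chi-square | ≥7 | 82.7% |
| 0.15 | 25 | exact one-sided | ≥8 | 69.4% |
| 0.15 | 32 | one-sided chi-square, or exact | ≥9 | 84.2% |

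For example, with n = 25 and reference 0.35 the standard error is √(0.35·0.65/25) = 0.0954. Then x = 12 gives z = (0.48 − 0.35)/0.0954 = 1.36 and x = 13 gives 1.78. Over all n from 25 to 32 the probability against 0.35 runs from 1.9% to 7.4%.

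**4. The opposite reading: support unless significantly below 0.35.** With n = 25, x = 4 gives z = −1.99 (significantly low) and x = 5 gives −1.57 (not), so 5 or more passes. At a true 0.15, P(X ≥ 5) = 32%. With n = 32 the cut-off is 7 (one-sided) or 6 (two-sided), and the pass rates are 19% and 35%.

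**5. One result, two p values.** For 8/25 (0.32), the exact one-sided p is P(X ≥ 8 | 0.15) = 0.025 and P(X ≥ 8 | 0.35) = 0.69. The one-sided chi-square gives z = 2.38 (p = 0.009) against 0.15 and z = −0.31 (p = 0.62) against 0.35.

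**The case against.** The strongest reply is that the analysis sentence never uses the word null. Its threshold is that of the alternative in the sample size section, so it may be shorthand for the hypothesis the trial hopes to support, with the null of 0.15 carried over. That may well be the intention. If so, the sentence still misnames the tested value and needs the same correction.

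The 3% to 6% is also, by construction, the type I error of a test whose null equals the true value. It follows from the reading and is not separate evidence for it. What it shows is that, read literally, the plan loses the power it was sized for.

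No passage requires significance above 0.35, and none counts non-significance below it as success. Both consequences are conditional on how the p value would be used. The stated decision rule concerns the observed proportion, but such a cut-off needs no chi-square test or p value, and the plan promises both. As a bare cut-off, 0.35 is reached at a true 0.35 only 53% of the time (≥9/25) or 45% (≥12/32), so it does not supply the planned 80% either.

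Finally, the trial is framed as estimating effect sizes, and a reader can compare the 95% CI with 0.15. This limits the practical harm but does not make the p value right. The article disclaims power only for comparing the arms, and it does power the single-arm test. The full protocol and analysis plan are not shown and may state the test correctly, but the contradiction here lies between two statements in the article itself.

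**Conclusion.** The concern holds and must be fixed. The sample size is correct for a null of 0.15, and the sentence defining the primary test gives 0.35 instead. Taken as written, with 25 or 32 everolimus patients analysed, a true proportion of 0.35 would be significantly above the reference value 2.5% to 6.0% of the time. The chi-square test the trial was sized for gives 83% to 84%.

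These figures take 0.35 as the null value, and they vary with the number analysed and the sidedness, as shown above. The contradiction between the two sections depends on none of these assumptions.

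**What to change.** In Main analysis, and in the analysis plan if it carries the same sentence, state that the test assesses whether the everolimus proportion improving by 1 SD at 6 months exceeds 0.15 (H0: p ≤ 0.15, one-sided alpha 0.05), and that the p value refers to 0.15. Keep 0.35 as the design alternative. If it is also to serve as a threshold on the observed proportion, describe that separately from the test.

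State the one-sided direction explicitly. A two-sided chi-square against 0.35 would also be significant for low proportions: at a true 0.15 this happens about 65% (n = 32) to 68% (n = 25) of the time. While the sentence is open, say whether the chi-square or the exact version governs. At n = 25 the one-sided chi-square against 0.15 rejects from 7/25 with a true type I error of 7.0%; the exact test rejects from 8/25 with 2.5%, at the lower power tabulated above.

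The cost is one sentence, settled before unblinding. Sample size, data collection, estimates and confidence intervals do not change.
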